# Community participatory learning and action cycle groups to reduce type 2 diabetes in Bangladesh (D:Clare trial): study protocol for a stepped-wedge cluster randomised controlled trial

**DOI:** 10.1186/s13063-021-05167-y

**Published:** 2021-03-29

**Keywords:** Diabetes, T2DM, Non-communicable diseases, Bangladesh, Participatory learning and action, Stepped-wedge trial

## Abstract

**Background:**

An estimated 463 million people globally have diabetes, with the prevalence growing in low-and middle-income settings, such as Bangladesh. Given the need for context-appropriate interventions to prevent type 2 diabetes mellitus (T2DM), the ‘Diabetes: Community-led Awareness, Response and Evaluation’ (D:Clare) trial will rigorously evaluate the replication and scale-up of a participatory learning and action (PLA) cycle intervention in Bangladesh, to inform policy on population-level T2DM prevention and control.

**Methods:**

This is a stepped-wedge cluster randomised controlled trial, with integrated process and economic evaluations, conducted from March 2020 to September 2022. The trial will evaluate a community-based four-phase PLA cycle intervention focused on prevention and control of T2DM implemented over 18 months, against a control of usual care. Twelve clusters will be randomly allocated (1:1) to implement the intervention at project month 1 or 12. The intervention will be evaluated through three cross-sectional surveys at months 1, 12 and 24. The trial will be conducted in Alfadanga Upazila, Faridpur district, with an estimated population of 120,000. Clusters are defined as administrative geographical areas, with approximately equal populations. Each of the six unions in Alfadanga will be divided into two clusters, forming 12 clusters in total. Given the risk of inter-cluster contamination, evaluation surveys will exclude villages in border areas. Participants will be randomly sampled, independently for each survey, from a population census conducted in January 2020. The primary outcome is the combined prevalence of intermediate hyperglycaemia and T2DM, measured through fasting and 2-h post-glucose load blood tests. A total of 4680 participants provide 84% power to detect a 30% reduction in the primary outcome, assuming a baseline of 30% and an ICC of 0.07. The analysis will be by intention-to-treat, comparing intervention and control periods across all clusters, adjusting for geographical clustering.

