### Sample size

The sample size was calculated using a presumed baseline combined prevalence of intermediate hyperglycaemia and T2DM of 30%, an assumed exchangeable correlation structure across surveys for each cluster, and an estimated intra-cluster correlation of 0.07. A sample of 110 participants per cluster, per survey, will give 84% power at 95% confidence to detect a minimum of 30% relative reduction in disease prevalence to 21% or less. An additional 10% was added to the sample size to allow for non-response, resulting in a total target sample of 3960. We will, in addition, include individuals identified with intermediate hyperglycaemia in subsequent surveys. We estimate 360 individuals will be identified as having intermediate hyperglycaemia at baseline and included in the month 12 and 24 surveys. The sample size was calculated using Stata SE14.

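### The abstract ties 84% power to 4680 participants, the Methods tie it to 110 per cluster per survey (3960), and the stated 10% non-response allowance is not visible in 3960

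*Protocol article*

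**What the plan says.** The abstract's Methods paragraph: "A total of 4680 participants provide 84% power to detect a 30% reduction in the primary outcome", with a baseline of 30% and an ICC of 0.07. The same paragraph describes participants as sampled at random and independently for each survey.

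The Sample size section uses the same prevalence and ICC but another number: "A sample of 110 participants per cluster, per survey, will give 84% power at 95% confidence". It continues: "An additional 10% was added to the sample size to allow for non-response, resulting in a total target sample of 3960". It then says that people found to have intermediate hyperglycaemia at baseline will be included on top of this, and puts them at 360, seen again at months 12 and 24.

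The Sampling section fixes the field procedure at 110 households per cluster, one eligible adult from each, with a fresh draw at every survey. It says the baseline intermediate-hyperglycaemia cases are selected purposefully for the later surveys. The Outcome section gives that group an outcome of its own, the cumulative incidence of T2DM.

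**The concern.** One power figure under one set of assumptions cannot belong to two totals that differ by 720 (4680 is 18% above 3960). The abstract is the most widely read part of the article, and its pairing is the one that fails.

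The Sample size section has a second problem of its own. It gives 110 as the number that delivers the power, says 10% was added, and arrives at a total with nothing added. A reader cannot tell whether 110 people must be analysed in each cell (cluster by survey) or only approached.

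Two things are at stake. One is the recruitment target that the Trial Steering Committee would monitor: 100 or 110 analysed per cell. The other is clarity about which records support the primary comparison, because a headline total that seems to include outcome-selected repeat visits blurs that boundary.

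**Working it through.** **Inputs.** Two-sided 5% (my reading of 95% confidence); prevalence falling from 30%, a "relative reduction in disease prevalence to 21% or less"; "an estimated intra-cluster correlation of 0.07"; "an assumed exchangeable correlation structure across surveys for each cluster" (all Sample size section). There are 12 clusters, 6 per sequence, and 3 surveys (Abstract; Design), so 36 cells with exposure patterns 0-1-1 and 0-0-1.

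**Step 1: the totals.**
- 36 x 110 = 3960. This is the stated total, with no addition.
- 110 inflated by 10%: 110 x 1.1 = 121 per cell, and 36 x 121 = 4356. Dividing by 0.9 instead gives 123 per cell, 4428.
- 110 already inflated: 110/1.1 = 100 per cell, and 36 x 100 = 3600 analysable.
- 3960 + 2 x 360 = 4680. This is the abstract's total exactly.

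**Step 2: power formula.** I used the Hussey-Hughes cross-sectional model with fixed survey effects and a random cluster effect. Let s be the individual-level variance divided by the number per cell, and t the between-cluster variance. For this design the variance of the effect estimate reduces to

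Var = s(s + 3t) / [3(s + 2t)]

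and power = Φ(0.09/√Var − 1.96).

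The article does not say how the binary variance was set, so I ran six conventions. The variance is taken at 30% (0.21), at the mean prevalence of 25.5% (0.190), or as the average of the variances at 30% and 21% (0.188). Each is treated either as total variance (t = 0.07 x variance) or as within-cluster variance (t = 0.07/0.93 x variance).

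**Step 3: reproduce the 84%.**
- 100 per cell, mean prevalence, within-cluster: s = 0.18998/100 = 0.0019, t = 0.0143, Var = 0.000930, SE = 0.0305, 0.09/SE = 2.951, power 83.9%. The averaged variance gives 84.3%.
- 110 per cell, variance at 30%, within-cluster: s = 0.21/110 = 0.00191, t = 0.0158, Var = 0.000936, SE = 0.0306, 0.09/SE = 2.941, power 83.7%.

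**Step 4: all conventions.**

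| Per cell | Total | Power, six conventions |
|---|---|---|
| 100 | 3600 | 80.1-86.8% |
| 110 | 3960 | 83.7-89.7% |
| 130 | 4680 | 89.1-93.8% |
| 110 / 140 / 140 by survey | 4680 | 90.2-94.6% |

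The last row places the extra 720 where the plan would put them, 360 in each later survey (30 per cluster). Both 4680 rows generously treat every record as a random draw.

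**Step 5: why the repeat visits cannot count.** They are selected for having a component of the primary outcome. As an upper-bound illustration, suppose all 360 kept their status and were pooled with 1320 random records at 30%. Prevalence in that survey would read (396 + 360)/1680 = 45%.

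**The case against.** The strongest defence is that this is a slip of reporting in a condensed abstract. The Sampling section gives field staff a clear instruction, the Sample size section introduces the repeat visits after and apart from the power sentence, and the Outcome section assigns them a separate outcome. Nothing tells anyone to recruit to 4680. If every record were a random draw, pairing 84% with 4680 would understate power. All of that stands, and it limits the consequences. It does not make the printed pairing correct.

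Several stronger readings are tempting and the article does not support them:
- A reader might infer three incompatible sample sizes. There are two printed totals, because 110 per cell and 3960 are the same number. The remaining question is whether 3960 is before or after non-response.
- A reader might infer that the 84% is wrong or the trial underpowered. It reproduces at 100 per cell and, under one convention, at 110. The lowest value at 100 is 80.1%.
- A reader might take 100 per cell (3600) as established. It is the likelier reading, because 110 is the number of households selected. A weak pointer is that 30% of 12 x 100 is 360, although 30% is the combined prevalence and not that of intermediate hyperglycaemia alone. The text literally attaches 84% to 110, and neither 100 per cell nor 3600 is printed.
- A reader might infer that the repeat visits will enter the primary analysis. The Analysis section includes everyone sampled in intervention periods, which read literally would admit them. Its example of repeated individuals concerns people drawn at random twice, which points the other way. The text does not settle it.

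**Conclusion.** Wrong as written, on two counts. First, 84% power does not belong to 4680: under the stated assumptions that total would give 89-94% spread evenly, or 90-95% with the extra records in the later surveys, and no convention gives 84%. Second, the statement that 10% was added to 110 to give 3960 is arithmetically false. Either 110 already contains the allowance, or the total should be about 4356.

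The planned random sample is not shown to be inadequate, and 84% is a plausible figure for it. That 4680 consists of 3960 plus 720 repeat visits is inferred from an exact sum.

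The power figures assume the exchangeable correlation that the article states, a normal approximation, and one of six variance conventions. Another reference distribution or correlation structure would shift them. The conflict between the two printed pairings, and the missing 10%, depend on none of these.

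**What to change.** In the abstract and the Sample size section:
- Attach the 84% to the analysable random sample.
- Have the sponsor confirm from the original calculation whether 100 or 110 per cell was powered, and make the non-response sentence and total follow. If it was 100, state 3600 analysable and 110 selected per cell, 3960 in all. If it was 110, state 3960 analysable and an inflated number of about 121 per cell, 4356 in all; the 110 households in the Sampling section would then need to be reconciled with that.
- Report the roughly 720 repeat visits on their own line as serving the cumulative-incidence outcome. State that they add no power to the primary prevalence analysis and are not counted in it.

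If the powered number was 100, this is a text correction with no change to design, allocation or sampling. If it was 110, the sponsor would also have to choose between sampling more households and stating the power expected after non-response.

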**Discussion:**

This study will provide further evidence of effectiveness for community-based PLA to prevent T2DM at scale in a rural Bangladesh setting. However, we encountered several challenges in applying the stepped-wedge design to our research context, with particular consideration given to balancing seasonality, timing and number of steps and estimation of partial versus full effect.

**Trial registration:**

ISRCTN: ISRCTN42219712. Registered on 31 October 2019

## Background

An estimated 463 million people globally have diabetes, with prevalence rising [1]. Currently, 75% of type 2 diabetes mellitus (T2DM) cases are thought to occur in low- and middle-income countries (LMICs) [2]. In South Asia, the increased incidence of diabetes has been attributed to rapid increases in income and urbanisation [3]. However, the prevalence of both T2DM and intermediate hyperglycaemia—including both impaired fasting glucose and impaired glucose tolerance—is also growing rapidly in rural areas [4]. This trend is seen in Bangladesh, with a rural community-based survey in 2016 finding more than one third of adults over 30 years of age had raised blood glucose levels [4].

T2DM is associated with a combination of behavioural risk factors, including sedentary behaviour and low physical activity, poor diet and smoking, alongside metabolic risk factors of hypertension, overweight and obesity, and genetic predisposition and gene-environment interactions [5]. Prevention and control efforts have predominantly targeted individual behaviour change amongst high-risk groups, with mixed results in South Asian settings [6–11].

There is a need to develop and test population-level interventions that create an enabling environment for the prevention of T2DM at scale, shifting from individualistic to structural and social interventions [12]. The DMagic (Diabetes Mellitus Action through community Groups or mHealth Information for better Control) trial used a participatory learning and action (PLA) approach directed at the general population in rural Bangladesh [13]. In this trial, significant increases in T2DM knowledge and awareness and reduced prevalence of T2DM and intermediate hyperglycaemia were reported. Amongst individuals identified with intermediate hyperglycaemia, the 2-year cumulative incidence odds of T2DM was 59% lower, equating to an absolute reduction of 21% for T2DM and 9% for intermediate hyperglycaemia. However, no significant changes were observed for diet, exercise and smoking behaviours. The intervention was highly cost-effective. Assuming a 30% loss of effectiveness at scale, an estimated 240,000 individuals could be prevented from developing T2DM and intermediate hyperglycaemia annually, with a cost-saving of INT$132 million [13].

Given the need for context-appropriate interventions to prevent T2DM at scale, the ‘Diabetes: Community-led Awareness, Response and Evaluation’ (D:Clare) trial will further inform policy on population-level T2DM prevention and control, through a large-scale implementation of PLA in rural Bangladesh.

## Methods

The aim of the D:Clare trial is to evaluate the scale-up of a PLA cycle intervention to prevent intermediate hyperglycaemia and T2DM and improve control of T2DM in rural Bangladesh.

We hypothesise that rapid horizontal scale-up of PLA will significantly (a) increase population-level awareness of diabetes prevention and control and (b) reduce the prevalence of intermediate hyperglycaemia and diabetes by at least 30%.

### Setting

The trial is set in Alfadanga Upazila, Faridpur district, in the central region of Bangladesh. Faridpur has an estimated population of 1.7 million and is divided into nine upazilas. Alfadanga was purposefully selected as the trial location as it is less liable to flooding and land erosion than other areas of Faridpur, has not been exposed to a PLA intervention previously and is close to an existing field office. Alfadanga has an estimated population of 120,000 people, divided into six administrative unions. The area is rural with a predominantly agricultural economy based on jute and rice; the population is mainly Bengali and Muslim, reflecting a ‘typical’ rural setting in Bangladesh [14].

Primary healthcare is provided at union health centres, family welfare centres and community clinics. Secondary care is provided at the upazila health complex, a charity-based diabetes centre in Alfadanga town, and the District Hospital in Faridpur town. There are two tertiary referral hospitals in the Faridpur district, which can treat T2DM complications.

### Design

This is a stepped-wedge cluster randomised controlled trial (SW-CRCT), with integrated process and economic evaluations (Fig. 1). Clusters are defined as administrative geographical areas, with a population of approximately 10,000. Each of the six unions in Alfadanga will be divided into two, forming 12 clusters. The SW-CRCT is at risk of inter-cluster contamination, where participants residing in clusters under control conditions may be exposed to the intervention in a neighbouring cluster. Therefore, we will use a ‘fried-egg’ design for our evaluation surveys, with participants residing in border areas excluded from surveys.

**Fig. 1 Fig1:**
[figure not shown]
Stepped-wedge trial design

The trial clusters will be randomly allocated, with a 1:1 ratio, to implement the intervention at either project month 1 or 12. The intervention will be evaluated with three cross-sectional surveys, at project months 1 (baseline), 12 (midline) and 24 (endline). The trial intervention period is planned to run for 30 months, from March 2020 to September 2022 (Fig. 1).

### Population

The intervention will be delivered at the community level to the whole population of Alfadanga Upazila, Faridpur district. The intervention will be available and accessible to any community member to participate, including health care providers. We will particularly encourage high-risk individuals, those aged over 30 years and those with T2DM to attend, as the groups we expect to benefit most from the intervention. The evaluation will include permanent residents—those who have lived within the study cluster for a minimum of 6 months, aged 30 years and older. The evaluation will exclude pregnant women.

### Intervention

The intervention is community mobilisation through PLA, focused on reducing intermediate hyperglycaemia and T2DM and improving non-communicable disease behaviours and risk factors. PLA works through community groups actively engaging communities in identifying the causes of health problems, and working together to design and implement ways to address these health problems, and reflect on their progress [15]. This approach has been shown to substantially improve maternal, neonatal and child health outcomes [16], and in the DMagic trial, reduce intermediate hyperglycaemia and T2DM [13].

The intervention and its theory base have been previously described [17–19]. Briefly, the intervention involves initiating separate men’s and women’s groups of 20–30 attendees. Separate groups are established to enable the participation of men and women that accounts for gender norms and convenient meeting times. Equal numbers of male and female groups are planned within communities, and groups will explore working together after approximately 10 months. The groups work through four phases of PLA: (1) problem identification where participants identify and prioritise causes of diabetes and diabetes risk in their community, (2) planning together where groups and communities collectively design strategies to address the causes of diabetes that can be implemented by communities, (3) strategy implementation and (4) participatory evaluation of the strategies which they have implemented. The four-phase cycle is planned to take 18 months, with groups meeting once a month. Those attending groups are encouraged to share information in communities and households and actively engage non-group attenders in their activities.

We plan for nine men’s and nine women’s groups in each cluster (*n* = 216 groups), for a coverage of 1 group per 200 adults aged 30 years and above. The groups will be led by trained and salaried facilitators, with one male and one female facilitator in each cluster; they will facilitate approximately nine meetings per month. All facilitators will have a minimum of secondary school education and will be recruited from the intervention areas. A 1-week training will cover group facilitation and basic health messages related to T2DM prevention and control. The facilitators will be provided with a community action manual, picture cards and flip charts developed through formative research during the DMagic trial. These materials are aligned with standard recommendations for the prevention of T2DM provided by the Diabetic Association of Bangladesh. The male groups will be led by a male facilitator, and the female groups will be led by a female facilitator. Facilitators will be mentored and supported by two participatory group coordinators and a district manager, based in Alfadanga, and a senior group intervention manager based in Dhaka. At the end of 18 months, a group volunteer will be trained in facilitation, and the groups will be encouraged to continue meeting.

### Control

During control periods, communities will receive standard diabetes prevention and care in accordance with usual practice in the region.

### Outcome

The primary outcome is the combined prevalence of intermediate hyperglycaemia (i.e. impaired fasting glucose and/or impaired glucose tolerance) and T2DM amongst adults aged 30 years or older, based on WHO definitions (Table 1) [20]. This is the same definition used in the DMagic trial.

**Table 1 Tab1:** WHO definition of normoglycaemia, intermediate hyperglycaemia and T2DM [20]

Definition	Diagnostic criteria
Normoglycaemia	Fasting plasma glucose ≤ 6.0 mmol/l
Intermediate hyperglycaemia	
Impaired fasting glucose	Fasting plasma glucose ≥ 6.1 mmol/l to < 7.0 mmol/l AND 2-h post-ingestion of 75 g glucose load plasma glucose < 7.8 mmol/l
Impaired glucose tolerance	Fasting plasma glucose < 7.0 mmol/l AND 2-h post-ingestion of 75 g glucose load plasma glucose ≥ 7.8 to < 11.1 mmol/l
Type 2 diabetes mellitus	Fasting plasma glucose ≥ 7.0 mmol/l OR* 2-h post-ingestion of 75 g glucose load plasma glucose ≥ 11.1 mmol/l

Secondary outcomes include the following: self-awareness of diabetes status, smoking prevalence, physical activity, mean population diastolic and systolic blood pressure, prevalence of hypertension (systolic blood pressure ≥ 140 mmHg or a diastolic blood pressure ≥ 90 mmHg or current treatment with antihypertensive medication), mean population body mass index, prevalence of overweight and obesity, mean population waist and hip circumference ratio, consumption of sugar, dietary diversity, knowledge of diabetes symptoms and complications, utilisation of diabetic services, psychological distress and ability to self-manage amongst diabetics. The cumulative incidence of T2DM amongst individuals with intermediate hyperglycaemia, identified during the survey at month 1 and followed up in subsequent surveys (at 12 and 24 months), will be calculated. Primary and secondary outcomes will be measured at months 1, 12 and 24 (Fig. 1).

### Randomisation

Due to the nature of the intervention, communities cannot be blinded to cluster allocation. Informed community consent will be taken through discussions with local leaders. Thereafter, clusters will be randomly allocated at a public meeting in the presence of traditional leaders and representatives from communities. The name of each cluster will be written on pieces of paper and folded uniformly by study staff, placed into a container and then drawn by a community representative. The clusters will be numbered in the order they are drawn, with clusters 1–6 implementing the intervention at month 1 and clusters 7–12 at month 12. The randomisation process will be filmed, with the consent of those present, to document the procedure.

### Sampling

Participants in the impact evaluation will be selected using a three-step sampling approach. Prior to randomisation, evaluation villages used for all cross-sectional surveys will be purposively selected using the following criteria: they do not sit on a border with a neighbouring study cluster; they are not a major trading centre or administrative centre; they have a minimum of 50 households. Between two and five villages will be selected, to achieve a total of 800–1000 households per cluster based on estimated population sizes from the 2011 Bangladesh census, and confirmed through rapid study census (Table 2, Fig. 2).

**Table 2 Tab2:** Estimated population per cluster, derived from the 2011 Bangladesh population census

Study cluster	Estimated cluster population	Estimated households in evaluation villages
Alfadanga 1	9891	923
Alfadanga 2	8827	1005
Bana 1	9345	970
Bana 2	8421	867
Buraich 1	11,386	1030
Buraich 2	13,047	813
Golpalpur 1	10,539	775
Golpalpur 2	9880	927
Panchuria 1	9257	706
Panchuria 2	9842	911
Tagarbanda 1	9628	812
Tagarbanda 2	10,450	736

